### Data Analysis

Descriptive statistics will be used to describe sodium and potassium intakes. Dietary sources of sodium and potassium will be determined at the individual level using the mean ratio method [84]. Liner and logistic regression models will be used to assess the association between electrolyte intake and health outcomes (blood pressure and BMI *z*-score and waist circumference) and to assess differences in taste preference and saltiness discrimination between food types, and correlations between taste preference, sodium intake, and covariates. To account for clustering of students within schools, clustered robust standard errors will be used. Analyses will be adjusted for covariates (age, gender, socioeconomic status).

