### Taste Testing Procedures

Tastings were conducted in one-to-one sessions using pre-packed, commercially available high and low salt variants of processed foods that have been identified as major sources of dietary sodium in Australian children (Table 2) [79]. A variety of different core food items such as bread, cereals, and cheese were evaluated. Within core food types tested, the difference in sodium content of the two samples varied between 27% and 84%. For example, one brand of bread with a sodium level of 202mg/100g was compared to another with 511mg/100g (60% difference). There were also differences in the percentage sodium variation within food categories, for example, processed meats varied between 25% and 40%, while for snack foods, potato crisps varied by 94% and tomato sauce by 27%. Differences in sodium content were calculated based on sodium levels provided on package nutrition information panels. To assess taste preference, children were asked to taste high and low salt samples of a food (Figure 2), and asked which they preferred using a forced choice methodology previously shown to be appropriate for use with children [80]. After this, they were asked which of the samples they thought tasted saltier. Participants were then asked to drink some water, and the same process was repeated with a second food type. The two food types tested, with two samples for each, were presented in unmarked wrapping in randomized order. Pairs of low and higher sodium foods were matched as closely as possible for appearance and nutritional composition other than sodium level.

**Table 2 table2:** Foods tested in sensory component.

Bread and cereal	Sandwich fillings	Snack foods
Bread: sourdough white; sourdough wholemeal^b^	Cheese, sliced cheddar^a^	Crisps, potato^a^
Wraps, multigrain^a^	Ham: sliced^a^	Corn chips, plain^a^
Cornflakes^b^	Chicken, sliced roast^a^	Rice crackers, plain^a^
Wheat cereal biscuits^a^		Baked beans^a^
		Tomato sauce^a^

^a^One-paired comparison, using low/high salt food variants.

^b^Two-paired comparisons, using low/high salt and medium/high salt food variants.

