## Results

Data collection was completed in May 2013. A total of 780 children across 43 schools participated. Data analysis is currently underway and results are expected at the end of 2015.

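### If taste is compared across the 12–13 individual foods with an ordinary joint Wald test on school-clustered errors from 43 schools, the false-positive rate is roughly 16–38% at a nominal 5%

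*Protocol article*

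**What the plan says.** Data Analysis (protocol article) plans linear and logistic regression "to assess differences in taste preference and saltiness discrimination between food types", adjusted for age, gender and socioeconomic status. One variance method covers all these models: "To account for clustering of students within schools, clustered robust standard errors will be used". Results gives the number of clusters: "A total of 780 children across 43 schools participated".

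Taste Testing Procedures describes a binary outcome for each food: children were "asked which they preferred using a forced choice methodology previously shown to be appropriate for use with children", and then said which sample was saltier. Each child did this for two foods: "The two food types tested, with two samples for each, were presented in unmarked wrapping in randomized order". In that sentence a food type is one food. Table 2 lists 12 foods; its first entry, "Bread: sourdough white; sourdough wholemeal", makes 13 if the two breads are separate. Two entries are marked as having an extra medium/high pair, so there are about 15 pairs.

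The Abstract words the comparison differently, as one between the higher- and lower-sodium foods. The article names no overall test, significance level, reference distribution or small-sample correction for the taste comparison, and it does not say how foods were allocated to schools.

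**The concern.** Forty-three clusters are usually enough for the standard error of one coefficient. A joint test across 12 or 13 foods is more demanding, because it inverts an 11×11 or 12×12 covariance matrix built from only 43 school score totals. The ordinary likelihood ratio test is not valid alongside clustered robust errors, so the test an analyst would normally run is the joint Wald test. Its usual chi-square or F reference treats that matrix as far better estimated than it is, and the test rejects too often.

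The taste comparison serves the fifth secondary aim. The Introduction ties it to food categories with sodium-reduction targets and to consumer acceptance of reformulated foods. A spurious finding that children's salt preference differs between foods would bear on that use.

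**Working it through.** **Inputs from the article.** G = 43 schools and 780 children (780/43 ≈ 18 per school); two foods per child; binary outcomes; 12 or 13 foods, so q = 11 or 12 (q = 14 if 15 pairs are compared, q = 2 if only the three Table 2 columns are).

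**Assumptions.** Nominal level 5%. The intra-cluster correlation (ICC) of 0.01 is the article's value for sodium, borrowed for taste; 0.05 was also tried. Spread of school sizes: coefficient of variation (CV) 0.05 to 0.8. The Phase 2 recruitment text makes uneven sizes likely: 11 schools had fewer than 10 participants, and consenting children per agreeing school averaged 269/9 ≈ 30 in Phase 1 against 582/47 ≈ 12 in Phase 2.

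**Plan's own figure.** There is none to reproduce. The only design calculation is for mean sodium.

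**Step 1: approximation.** Under no food difference, the joint Wald statistic W behaves roughly like Hotelling's T²: W × (G−q)/[q(G−1)] follows F(q, G−q).

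For q = 12 the scale factor is 31/(12 × 42) = 0.0615.
- Chi-square reference: critical value 21.03; 21.03 × 0.0615 = 1.293; P[F(12, 31) > 1.293] = 27.1%.
- F(12, 42) reference: critical value 12 × 1.991 = 23.89; 23.89 × 0.0615 = 1.470; P[F(12, 31) > 1.470] = 18.9%.

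| q | Chi-square reference | F(q, 42) reference |
|---|---|---|
| 2 (three groups) | 6.5% | 5.4% |
| 11 (12 foods) | 23.8% | 16.5% |
| 12 (13 foods) | 27.1% | 18.9% |
| 14 (15 pairs) | 34.8% | 24.7% |

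**Step 2: simulation under no food difference.** 1,000 runs per row, logistic model with food indicators and covariates, school-clustered sandwich variance with the G/(G−1) factor. ICC is 0.01 and size CV 0.5 unless stated. Foods are drawn at random for each child except in the last three rows. At a rate of 30% the Monte Carlo standard error is √(0.3 × 0.7/1000) ≈ 1.4 points.

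| Scenario | Joint, chi-square | Joint, F(q, 42) | Joint, scaled F(q, G−q) | One food contrast (normal) |
|---|---|---|---|---|
| 13 foods, near-equal schools | 24.2% | 17.0% | 3.6% | 5.4% |
| 13 foods, size CV 0.5 | 30.0% | 22.4% | 6.1% | 4.3% |
| 13 foods, size CV 0.8 | 38.3% | 29.5% | 10.6% | 6.1% |
| 13 foods, ICC 0.05 plus child effect | 30.5% | 20.9% | 6.2% | 6.6% |
| 12 foods, size CV 0.5 | 29.9% | 21.9% | 7.5% | 5.8% |
| 3 groups, size CV 0.5 | 6.1% | 3.9% | 3.7% | 5.7% |
| 13 foods, each school sees 6 | 37.7% | 30.0% | 11.4% | 8.1% |
| 13 foods, each school sees 4 | 43.4% | 32.9% | 14.1% | 7.8% |
| 13 foods, each school sees 2 | 66.0% | 58.4% | 40.3% | 12.3% |

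(986 runs were usable in the last row.) A linear model gave similar joint chi-square rates: 36.1% for 13 foods, 28.8% for 12 and 7.5% for three groups.

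**Step 3: the alternative test.** Separate null simulations used 43 schools, about 780 children, 13 foods, and assumed school and child SDs of 0.3 and 0.5 on the logit scale. A null-imposed score test that flips the signs of school score totals rejected 5.2%, 5.3%, 4.3% and 5.7% in four scenarios: equal or unequal school sizes, and foods varied within school or rotated by school. A further check found 5–7% throughout.

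**The case against.** The strongest objection is that the article does not name the criticised test. It fixes standard errors, not a joint hypothesis, and for single coefficients those standard errors work. The test statistic and its reference distribution are details that a condensed article may leave to an analysis plan, and none is shown here. That stands, and it makes the point conditional. The article does, however, name both the comparison and the variance method, and the ordinary joint test from that pair is badly sized.

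The hypothesis can also be read otherwise. The Abstract contrasts higher- with lower-sodium foods, Table 2 has three columns, and the aim could be met by estimates for each food with no overall test. Those readings are open, and on them the problem largely disappears. The wording of Taste Testing Procedures favours the individual-food reading but does not settle it.

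A reader might infer that the planned analysis carries a false-positive rate of 27% or more. The documents do not support that. The 27% belongs to one case (13 foods, chi-square reference), and the tables above contain lower values. Nor can the rates for few foods per school be taken as the study's own, since allocation is not stated.

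Finally, sodium gaps within pairs run from 25% to 94%, so identical saltiness discrimination across foods is an unlikely null. That weakens the practical harm for discrimination. It says less about preference, and in either case the overall p-value would overstate the evidence. Some children were also excluded from tasting, so 780 is an upper figure.

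**Conclusion.** The point holds conditionally. If food types means the 12–13 individual foods, and equality across them is tested with the ordinary joint Wald test, the false-positive rate at an assumed 5% is roughly 16–38%. The low end is 12 foods with the F(q, 42) reference (16.5%); the high end is 13 foods with chi-square and very uneven schools (38.3%). It can be higher if each school tasted only a few foods. Single-food contrasts are sound when foods vary within school (about 4–7%), and a three-group comparison is near nominal (about 6–8% with chi-square).

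The cause is the number of parameters tested relative to the number of schools, not the choice to cluster on school. The ICC, the spread of school sizes, the 5% level and food allocation are assumptions. This is a worthwhile correction for a secondary aim, not an unconditional error in the plan.

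**What to change.** State what the food comparison tests: individual foods, Table 2 groups, or higher against lower sodium. Keep the logistic model, and keep school-clustered errors for single-food contrasts. Test any multi-food hypothesis with a null-imposed school-level score test or a wild cluster bootstrap.

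At minimum, multiply the Wald statistic by (G−q)/[q(G−1)] and refer it to F(q, G−q). For 13 foods this raises the critical value of W from 21.03 to 33.82 (2.080/0.0615). It removes most but not all of the excess, leaving roughly 5–10% with foods varied within school (3.6% to 10.6% in the 12- and 13-food runs shown), and it is not enough if each school saw very few foods. If foods were rotated by school, use the score or bootstrap test for single-food contrasts too.

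The cost is a sentence or two in the analysis plan and a few lines of code, with no new data; Results says analysis was still underway. The downside is fewer significant overall food differences.

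### The adjustment set stated for the taste preference–sodium intake analysis omits food pair, although the article expects preference to differ by food; adding it is a small, nearly free gain

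*Protocol article*

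**What the plan says.** The Data Analysis section of the protocol article puts two taste questions into one sentence. Linear and logistic models are to be used "to assess differences in taste preference and saltiness discrimination between food types", and also for "correlations between taste preference, sodium intake, and covariates". Errors are clustered by school. The section then fixes the covariates: "Analyses will be adjusted for covariates (age, gender, socioeconomic status").

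Taste Testing Procedures describes what each child did: "The two food types tested, with two samples for each, were presented in unmarked wrapping in randomized order". Randomisation is attached to presentation order; how foods were allocated to children is not described. Table 2 marks most foods "One-paired comparison, using low/high salt food variants", and bread and cornflakes "Two-paired comparisons, using low/high salt and medium/high salt food variants". For core foods, "the difference in sodium content of the two samples varied between 27% and 84" per cent; elsewhere, "processed meats varied between 25% and 40%, while for snack foods, potato crisps varied by 94% and tomato sauce by 27" per cent.

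The Introduction, under Preference for Salt Taste in Children, notes that how salty people like a food to be depends on the food.

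**The concern.** Choosing the saltier of two crisps that differ by 94% in sodium is not the same outcome as choosing the saltier of two tomato sauces that differ by 27%. With two food types per child, a child's recorded preference depends partly on which pairs that child was given. The article treats food as a source of variation when it compares foods, but its covariate list for relating preference to sodium intake has no food term. School-clustered errors change the standard error and leave the point estimate alone.

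At stake is the size and precision of a secondary association. If choices are combined over foods, differences in base preference between pairs bring the odds ratio closer to 1 and cost a little power.

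**Working it through.** **1. The article's own contrast figure.** Bread is given as 202 against 511 mg/100 g, stated as a 60% difference. 1 − 202/511 = 0.605, so it reproduces.

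**2. Number of pairs (Table 2).** Ten foods have one pair: wraps, wheat biscuits, cheese, ham, chicken, crisps, corn chips, rice crackers, baked beans and tomato sauce. Bread and cornflakes have two.
- Bread counted once: 10 × 1 + 2 × 2 = 14.
- White bread with one pair and wholemeal with two: 10 + 1 + 2 + 2 = 15.
- Both breads with two pairs: 10 + 2 × 3 = 16.

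So there are at least 14 pairs.

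**3. Choices available.** From the section on completeness of urine samples: 757 results − 90 invalid = 667. Two choices each give 667 × 2 = 1,334. Spread evenly, that is 1,334/14 = 95 per pair, or 1,334/16 = 83. The figure 780 × 2 = 1,560 would count children without a valid sodium value. Allergy exclusions from tasting reduce 1,334 further by an unstated number.

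**4. Effect of leaving pair out.** The article gives no preference rates by food, so the spread between pairs is assumed. Closed-form approximation: the log odds ratio without pair divided by that with pair ≈ 1/√(1 + 0.346·s²), where s is the SD of the pair log-odds.

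Simulation: 667 children, two choices each, 43 schools, 14 pairs, sodium ICC 0.01 (the planning value), conditional odds ratio 1.30 per SD of sodium (assumed), 150 data sets per setting. Entries are the mean log odds ratio without pair indicators divided by the true value.

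| s | Closed form | Foods random by child | Foods by school, unrelated to sodium | By school, correlation 0.5 with school-mean sodium | By school, perfect tracking |
|---|---|---|---|---|---|
| 0.25 | 0.989 | 0.973 | 0.974 | 1.022 | 1.053 |
| 0.5 | 0.959 | 0.955 | 0.941 | 1.013 | 1.040 |
| 1.0 | 0.862 | 0.828 | 0.851 | 0.949 | 1.042 |

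With pair indicators the odds ratio was 1.295 to 1.310 throughout. Where foods are unrelated to sodium, the shrinkage is 1 − 0.974 ≈ 3% up to 1 − 0.828 ≈ 17% (closed form 1% to 14%). Simulation error is roughly 1/√(1,334 × 0.25)/√150 = 0.0045 on a log odds ratio of 0.262, or 1.7%, so the low end is hard to tell from 1%.

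**5. Power.** Separate simulations used a true log odds ratio of 0.20 per SD, 14 pairs and 400 data sets per scenario.
- Base preference for the saltier variant from 25% to 85%, foods by school, 43 × 18 children: estimate 0.172 without pair and 0.202 with; power 89% against 94% (a repeat run gave 91% against 94%).
- Same spread, 667 children: 0.173 against 0.203 and power 89% against 91% with foods by school; 0.178 against 0.209 and 87% against 92% with foods random by child.
- Spread from 40% to 70%: 0.197 against 0.206, a difference of 1 − 0.197/0.206 ≈ 4%; power 96% with and without pair in the repeat run.
- No true effect, model without pair: rejection 3.8% and 4.5% under the two spreads.

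**The case against.** The strongest reply is that the article nowhere says choices are pooled. The same sentence already names food type as a contrast, and a condensed article may leave the handling of foods to a fuller plan that is not shown. This stands in part: pooling is an inference and is not asserted here. But the food-type clause answers a different question, and the covariate list is a positive statement without a food term.

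The model form is also presumed. The article does not say that preference is the outcome or that the single choice is the unit. If sodium is the outcome, or preference is scored per child, the percentages above do not carry over.

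The shrinkage is largely non-collapsibility. The smaller value is the odds ratio averaged over the foods served and the larger is conditional on pair: two estimands, neither of them an error. That is correct. The case for the conditional one is that the averaged one depends on the mix of foods served as well as on the children.

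Two stronger readings are tempting. A reader might infer that a null result would be an artefact of the food mix. The figures do not support this: the test stays valid under no effect, and a loss of 0–5 points of power does not manufacture a null.

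A reader might also infer that food allocation distorts the association. The Participants section does bar children with specific allergies from the relevant foods, so allocation was not wholly free of child characteristics. But nothing in the article links allocation to sodium intake. With perfect tracking at ICC 0.01 the net error was 4–5%, and upward. That net figure hides an offset: at s = 1.0, moving from no tracking to perfect tracking shifts the ratio from 0.851 to 1.042. Confounding is therefore possible but not shown.

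Finally, the preference–intake relation is not among the five secondary aims listed in the Introduction; it appears only in the Abstract and Data Analysis. That lowers the priority.

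**Conclusion.** The point holds as a low-severity improvement to a secondary analysis. The stated covariates omit a factor that the article itself expects to affect preference, and no by-food analysis of the intake question is stated. If choices on different foods are combined in a logistic model for preference without food pair, the log odds ratio is attenuated by roughly 3–17%, with about 0–5 points of power lost. Those sizes rest on assumed spreads in base preference, assumed effects of 1.30 per SD (odds ratio) or 0.20 per SD (log odds ratio), and the planning ICC of 0.01. The true spread is unknown from the document. The article does not support a claim that it commits to pooling, that a null finding would be false, or that the association is confounded.

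**What to change.** In the models relating taste preference and saltiness discrimination to sodium intake and covariates, add food pair as a fixed effect. Use one level per pair rather than per food, so that low/high and medium/high versions of bread and cornflakes are separate. Stratifying by pair, for example with conditional logistic regression, is an alternative. Keep the school-clustered standard errors, and state how a child's two choices enter the model.

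With 14 pairs this uses 14 − 1 = 13 degrees of freedom (15 with 16 pairs) against about 1,334 choices. No new data are needed.

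Pair indicators remove only differences in base preference. If the association itself may vary with the sodium contrast, a by-food or interaction analysis is also needed. One sentence on how foods were allocated to children would settle whether confounding needs further thought.

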### Association Between Sodium and Potassium Intake and Cardiovascular Risk Factors

The dietary electrolytes, sodium and potassium, are both involved in the development of high blood pressure [30]. In adults, excess dietary sodium has a detrimental effect on blood pressure [7] and cardiovascular health [31], whereas higher intake of potassium has been shown to be protective [32]. The interplay between these two electrolytes is important, with the sodium to potassium ratio associated with blood pressure [33,34] and a predictor of cardiovascular disease (CVD) risk [35]. During childhood, sodium and potassium are also important moderators of blood pressure. The evidence for the effects of sodium intake on blood pressure in children and adolescents is strong. Population studies from the United Kingdom [36] and the United States [37,38] have reported a positive association between sodium intake and blood pressure. Furthermore, findings from meta-analyses have shown that reductions in sodium intake lead to modest reductions in blood pressure [4,39].

Findings relating to the effects of potassium alone on blood pressure in children and adolescents are less consistent. For example, some cross-sectional studies have found either a positive association [11,40] or inconsistent findings by gender [41] between potassium intake and blood pressure. Conversely, longitudinal studies have found that a higher intake of potassium is associated with lower systolic blood pressure [6,42]. A recent meta-analysis, which included three intervention trials and one cohort study, found no association between potassium intake and blood pressure levels in children [43]. The World Health Organization’s most recent guideline for potassium intake in children acknowledges the inconsistencies across studies in children. However, given the protective effects of potassium on blood pressure and CVD risk in adults, it is recommended that children’s potassium intake be in line with the recommendation for adults (ie, at least 90 mmol/d or 3510 mg/d) with adjustment for energy requirements [44]. Most studies in children have examined the effects of either sodium or potassium on blood pressure in isolation. One longitudinal study in Dutch children found that although sodium alone was not related to blood pressure, a higher sodium to potassium ratio was predictive of higher systolic blood pressure levels [6].

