### Additional Risks of High Sodium Intake During Childhood

Beyond the concerns of high sodium diets raising blood pressure, there is evidence in children to indicate that higher intake of sodium is associated with increased risk of overweight and obesity. There are now data from three large population-based nutrition surveys in children and adolescents (ie, Great Britain [47], Australia [48], and the United States [49]) that support the link between dietary sodium intake and obesity via greater consumption of sugar-sweetened beverages (SSBs). Remarkably similar results have been observed across each country whereby sodium intake was positively associated with SSB consumption, which in turn is an important risk factor for obesity [50]. However, more recent evidence suggests that sodium intake is associated with adiposity, independent of energy intake [51]. To date, no study has utilized a reliable marker of sodium intake (24-hour urinary sodium excretion) to examine the association between sodium intake and measures of adiposity in Australian children. As overweight and obesity follows a trajectory over the life course [52], it is important to understand the association between these risk factors and 24-hour urinary sodium excretion in Australian children.

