### The Salt and Other Nutrient Intakes in Children (SONIC) Study

The primary aim of the SONIC study was to obtain an accurate measure of total dietary sodium intake using 24-hour urinary excretion in a sample of primary schoolchildren in Victoria, Australia. Secondary aims within this sample of primary schoolchildren were: (1) to objectively measure potassium intake and the sodium to potassium ratio using 24-hour urinary electrolyte excretion, (2) to identify the dietary sources of sodium and potassium, (3) to assess the association between 24-hour urinary sodium and potassium excretion and blood pressure, (4) to assess the association between 24-hour urinary sodium excretion and body mass index (BMI) z-score and waist circumference, and (5) to identify children’s taste preferences and saltiness perception using high and low sodium variants across a range of manufactured foods, which are major dietary sources of salt.

The purpose of this paper is to describe the study design and data collection methods used within the SONIC study. In addition, we report on the recruitment outcomes and data processing procedures for determining completeness of 24-hour urine samples within the study population.

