### Testing Procedures

An overview of data procedures completed is shown in Table 1.

**Table 1 table1:** Overview of data collected.

Item		Description
Health and medical questionnaire		Child’s date of birth, gender, birth weight, health conditions, medications, dietary supplements, discretionary salt use habits, parent’s highest level of education attained
Anthropometry		Height, weight, body mass index, waist and hip circumference
Blood pressure		Systolic and diastolic blood pressure
24-hour urine collection		Urinary sodium, potassium, creatinine, total volume
24-hour dietary recall		Food and beverage intake, table salt use
Taste testing		Preference and discrimination with high vs lower salt food item

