### Blood Pressure

Blood pressure was measured using an automatic vital signs monitor (OMRON HEM-907) machine according to the US National Heart Lung and Blood Institute Guidelines [72]. Measurements were completed in the sitting position after 10 minutes of rest with the child’s arm positioned at the level of the heart on a rested table. Children were instructed to refrain from talking or coughing during the measurements. To determine the appropriate cuff size, the child’s upper arm (midpoint between the acromion and olecranon) circumference was measured and from this one of three cuff sizes (small 17-22 cm, medium 22-32 cm, large 32-42 cm) was selected for use. The cuff was positioned on the child’s arm by aligning the marked cuff artery indicator with the brachial artery. Once wrapped firmly on the arm, the cuff size was checked by ensuring the marked index line fit within the specified range line on the cuff. If the cuff was noted as being too small or too large, the size up or down was fitted. Three blood pressure readings were taken on the right arm at 1-minute intervals. The average of the last two measurements will be used for analysis.

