#### Urinalyses

Urinary sodium and potassium concentration was assessed using indirect ion selective electrodes and urinary creatinine concentration was assessed using the Jaffe reaction [81] on the Siemens Advia 2400 analyzer (Dorevitch Pathology, Melbourne, Vic, National Association of Testing Authorities and Royal College of Pathologists of Australia accredited pathology laboratory). Per participant 2 x 10 mL aliquots were taken for storage and transferred to −80 ^°^C conditions. The molecular weights of sodium (23 g/mol), sodium chloride (58.5 g/mol), and potassium (39.1 g/mol) will be used to convert laboratory of mmol to mg [18].

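### The blood pressure models adjust for age, gender and socioeconomic status but not for body size, so the sodium and potassium slopes may be confounded, most clearly by height

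*Protocol article*

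**What the plan says.** The Data Analysis section of the protocol article plans regression models to "assess the association between electrolyte intake and health outcomes (blood pressure and BMI *z*-score and waist circumference", with the same paragraph also covering taste preference and saltiness discrimination. One adjustment sentence follows for all of these: "Analyses will be adjusted for covariates (age, gender, socioeconomic status".

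The blood pressure models serve secondary aim 3: "to assess the association between 24-hour urinary sodium and potassium excretion and blood pressure".

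Two other sections fix the scales. Under Urinalyses, molecular weights "will be used to convert laboratory of mmol to mg", so excretion stays an absolute daily amount. Normalisation under the completeness criteria is to 24 hours, not to body weight. Under Blood Pressure, "The average of the last two measurements will be used for analysis", with no standardisation for height.

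Body size was measured. Table 1 lists "Height, weight, body mass index, waist and hip circumference". In the planned regressions, BMI z-score and waist appear only as outcomes, and height does not appear as a covariate.

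**The concern.** A larger child needs more energy, eats more, and so excretes more sodium and potassium per day. If a larger child also has higher blood pressure, body size links exposure and outcome without any effect of the electrolytes. Age and gender remove part of this, but children of the same age and gender still differ in height and weight.

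The article supports the exposure side of the link. Its section on additional risks reports evidence that "sodium intake is associated with adiposity, independent of energy intake". Its discussion of potassium scales the recommendation for children to energy requirements. Its Dietary Recall section estimates basal metabolic rate from weight and height as well as age and gender, so age and gender alone do not capture energy need.

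At stake is the reading of aim 3. A sodium slope could partly reflect body size, and the potassium slope could be pushed in the positive direction. The article describes the potassium evidence in children as inconsistent, so such a shift would matter there too.

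**Working it through.** **The plan's own figures.** The article gives no calculation for the blood pressure models. Its sample size is for mean sodium and reproduces: (1.96 × 37 / 4)² = 328.7, so 329; × 1.09 = 358.6, so 359; × 1.10 = 394.9, so 395. That calculation does not bear on the covariates. It supplies only two inputs used below.

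**Inputs from the article**
- Sodium SD 37 mmol/d and intra-cluster correlation 0.01 (Sample Size).
- Valid urines: 757 − 90 = 667 (Criteria for Assessing Completeness of 24-Hour Urine Samples).
- Schools: 43 (Results).

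**Inputs assumed, because the article gives none**
- r: correlation of measured sodium excretion with body size, given age, gender and socioeconomic status; 0.1 to 0.4.
- b: standardised slope of blood pressure on body size, given sodium and the same covariates; 0.1 to 0.4.
- Blood pressure SD: 8 to 11 mmHg.

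**Bias.** When body size is left out, the standardised sodium slope is shifted by b × r. The same expression holds for potassium with its own r. If r = 0 the bias is zero.

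**Consequence for a test.** Suppose the true slope is zero.
- Average cluster: 667 / 43 = 15.5.
- Approximate design effect: 1 + (15.5 − 1) × 0.01 = 1.145.
- Standard error of the standardised slope: √[(1 − (b × r)²) × 1.145 / 661], where 661 = 667 − 6. This is about 0.041 to 0.042 over the range.
- z = (b × r) / SE, and the rejection probability at two-sided 5% is Φ(z − 1.96) + Φ(−z − 1.96).

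For r = b = 0.3: bias 0.09, SE 0.0415, z = 2.17, rejection probability 0.58.

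| r = b | Bias (SD of blood pressure per SD of sodium) | mmHg per 37 mmol/d, SD 8 | mmHg per 37 mmol/d, SD 11 | Rejection probability (nominal 0.05) |
|---|---|---|---|---|
| 0.1 | 0.01 | 0.08 | 0.11 | 0.06 |
| 0.2 | 0.04 | 0.32 | 0.44 | 0.16 |
| 0.3 | 0.09 | 0.72 | 0.99 | 0.58 |
| 0.4 | 0.16 | 1.28 | 1.76 | 0.97 |

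The mmHg columns treat 37 mmol/d as the sodium SD given the covariates, which is an approximation.

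**The case against.** The strongest reply is that the adjustment sentence is a summary covering every regression, including those with BMI z-score as outcome, where BMI could not be a covariate. It could be the common set, with outcome-specific covariates left to a fuller plan. That reading is possible and lowers confidence. But the sentence names its covariates without marking them as examples, and nothing elsewhere in the article brings body size into the blood pressure models.

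The second reply is mediation, and it stands for BMI. The section on additional risks describes a route from sodium through sweetened drinks to obesity. On that route, leaving BMI out is legitimate for a total association. A reader might infer that everything carried by BMI is spurious; the article does not support that. Height is not on the route described, so for height the reply does not help.

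Third, a reader might infer that the reported slope will be too high on balance. The article does not establish this. It says that a single collection varies widely from day to day and that at least seven are needed for an individual's intake. That error would attenuate a true slope, so the net direction is open.

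Fourth, since the article remarks that "Most studies in children have examined the effects of either sodium or potassium on blood pressure in isolation", a reader might infer that it repeats the fault by not adjusting each electrolyte for the other. The Data Analysis section does not say whether they enter jointly or separately. That silence is ordinary in a condensed article and is no defect. Nor does the article give grounds for calling collection day or school sector omitted confounders.

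**Conclusion.** The point holds in a limited form. Followed as written, the blood pressure models leave differences in body size among children of the same age and gender uncontrolled, most clearly height, and do not say whether a total or a direct association is meant with respect to BMI.

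The size is not known. It depends wholly on the assumed conditional associations and blood pressure SD, and on a link between body size and blood pressure that the article does not state. Over the assumed range the effect goes from ignorable to enough to produce a significant slope on its own. The table should not be read as a prediction within that range.

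Aim 3 is secondary. Mean sodium and potassium excretion, their ratio and the dietary sources are descriptive and untouched. This should be fixed, but it does not threaten the primary result.

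**What to change.** For systolic and diastolic pressure only, replace the covariate set with age, gender, socioeconomic status and height, or keep the present set and use a height-standardised blood pressure outcome. Report the sodium and potassium slopes from this model without and with BMI z-score. State in advance that the slope without BMI z-score is read as the total association and the slope with it as the direct association, because the article allows BMI to be a mediator.

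Do not add BMI z-score to the models in which BMI z-score or waist circumference is the outcome.

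The cost is a sentence or two in the analysis section and one extra model for each blood pressure outcome. All the variables are already collected. The Results section says analysis is under way, so the choice should be recorded before the blood pressure slopes are examined.
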